#### Laboratory analyses

In the first part of the study, we conducted diagnostics regarding acute SARS-CoV-2 infection with real-time quantitative PCR and SARS-CoV-2 Antibody diagnostics with ELISA as described in our previous publication (Table 1) [19, 22].

Serological tests of the second part of the study will be based on dried blood spots (DBS) as sample material for the follow-up testing (Table 1). The EUROIMMUN blood collection kit (ZV 9701–0101) allows convenient sampling at home. Capillary blood will be self-collected from the fingertip and applied onto blood collection cards. The five circles on the card have to be filled as completely as possible, and the blood droplets are left at room temperature for 3–4 h to dry. Afterwards, the card will be shipped to our laboratory for analysis. DBS will be punched out of the blood collection card for analysis, and the sample is then extracted from the DBS. The ELISA will be performed as previously described [19].

The second part also involves testing for other respiratory viruses (Table 1). Trained staff will take a nasopharyngeal swab (eSwabTM, COPAN) from a subset of 500 participants that will be invited to come to the study center. Swabs will be processed for nucleic acid extraction using the NucliSens® easyMAG™ platform (Biomérieux), according to the manufacturers’ instructions. Nucleic acids will be eluted, and quantitative RT-PCR is performed according to the manufacturers’ instructions using the *ampli*Cube Respiratory Viral Panel 1, 3, 4 and the *ampli*Cube Coronavirus Panel Kits (MIKROGEN, Neuried). Respiratory viruses include influenza A/B, SARS-CoV-2, MERS-CoV, hCoV (229E, HKU1, NL63, OC43), parechovirus, RSV, metapneumovirus, rhinovirus, enterovirus, and adenovirus.

### Statistics

#### Sample size calculation

No formal sample size calculation was made. With the resources available, it seemed possible to examine approximately 3000 individuals. We aimed for at least 1500 population-based participants and 1500 persons at risk, allowing overlap between both groups.

When planning the study, an official COVID-19 prevalence of 120/100,000 inhabitants was reported for the study region (Robert Koch Institute, April 27th, 2020). The true prevalence was assumed to be 5-fold higher (600/100,000) [23]. Based on a 1500 person sample a population-based infection prevalence rate of 0.60% with a 95% confidence interval of 0.31–1.05% could be determined. The precision of such an estimate seemed appropriate to us.

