### Study procedures

#### Recruitment and sample

Initial cohort recruitment took place in April 2020 via local press and radio announcements, posters, flyers, an announcement by the mayor of Luebeck on the city’s official homepage, as well as University internal e-mail distribution. Inclusion criteria comprised residence in the metropolitan area of Luebeck, age 18 years or older, active consent for study participation, registration for study participation via the study app, and willingness and ability to come to the local study test center for regular PCR testing and antibody measurements. Study registration and consent were app-based, using an existing cell phone app (MillionFriends, Perfood GmbH) established by a start-up company that emerged from the University of Luebeck (see below).

Activation of the study app marked the start of the study and, based on the information provided in the initial questionnaire (e.g., age, occupation, gender), a sample representative of the Luebeck population (*n* = 2145) was drawn from 7303 registered individuals, as well as a risk group consisting of individuals with a high number of professional contacts with other people (*n* = 1374). Ultimately, 3474 individuals were selected and invited via an e-mailed link to make the first appointment at the study test center using an online appointment booking app.

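### The printed 95% interval of 0.31–1.05% does not follow from 0.60% in 1500 people; the sample size or the confidence level appears to be mislabelled

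*Protocol article*

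**What the plan says.** All the relevant text is in the protocol article, Statistics, Sample size calculation. The section says that no formal calculation was made and that available resources pointed to about 3000 people. It sets the recruitment aim: "We aimed for at least 1500 population-based participants and 1500 persons at risk, allowing overlap between both groups".

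It then illustrates precision. The starting point is that "an official COVID-19 prevalence of 120/100,000 inhabitants was reported for the study region". The next step is "The true prevalence was assumed to be 5-fold higher (600/100,000"). From this follows the sentence at issue: "Based on a 1500 person sample a population-based infection prevalence rate of 0.60% with a 95% confidence interval of 0.31–1.05% could be determined". The authors conclude: "The precision of such an estimate seemed appropriate to us".

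The interval method is not named, and no other precision figure appears in the article.

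**The concern.** The sentence supplies every input to a textbook calculation (prevalence, sample size and confidence level) and then prints a result that these inputs do not give. The printed interval is narrower than the stated design delivers, so the error favours the study.

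Two things are at stake. First, the authors' judgement that precision is adequate refers to this interval alone. Second, one study aim is to estimate the extent of undetected infections, and the article offers its design as a template for other regions. A group that plans for 1500 people and expects a 95% interval of 0.31–1.05% will not obtain it.

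**Working it through.** **Inputs (Sample size calculation section)**
- Official prevalence 120/100,000; assumed true prevalence 5 × 120 = 600 per 100,000 = 0.60%. This step is correct.
- n = 1500, so the expected positives are x = 0.006 × 1500 = 9 exactly, and rounding of the count plays no part.
- Level 95%, taken as two-sided because the article does not say.
- Printed interval 0.31–1.05%, width 1.05 − 0.31 = 0.74 percentage points.

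**Step 1. Try to reproduce the printed interval at 9/1500.** The exact (Clopper-Pearson) limits are the 2.5% quantile of Beta(x, n − x + 1) and the 97.5% quantile of Beta(x + 1, n − x). With x = 9 and n = 1500 these are Beta(9, 1492) and Beta(10, 1491), which give 0.2747% and 1.1359%. The exact Poisson limits are the 2.5% quantile of chi-square with 2x degrees of freedom and the 97.5% quantile with 2x + 2 degrees of freedom, each divided by 2n. The results for these and ten other methods are:

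| Method, 95%, 9/1500 | Limits (%) | Width | Width / 0.74 |
|---|---|---|---|
| Clopper-Pearson | 0.275–1.136 | 0.861 | 1.16 |
| Exact Poisson | 0.274–1.139 | 0.865 | 1.17 |
| Wald | 0.209–0.991 | 0.782 | 1.06 |
| Likelihood ratio | 0.289–1.079 | 0.790 | 1.07 |
| Jeffreys | 0.297–1.092 | 0.795 | 1.07 |
| Mid-P | 0.293–1.098 | 0.805 | 1.09 |
| Wilson | 0.316–1.136 | 0.820 | 1.11 |
| Arcsine | 0.273–1.054 | 0.781 | 1.06 |
| Logit | 0.312–1.149 | 0.837 | 1.13 |
| Log | 0.313–1.151 | 0.838 | 1.13 |
| Agresti-Coull | 0.297–1.155 | 0.858 | 1.16 |
| Wilson, continuity-corrected | 0.293–1.180 | 0.887 | 1.20 |

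No row rounds to 0.31–1.05, and every row is wider than 0.74. Logit and log match the lower limit only; arcsine matches the upper limit only.

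**Step 2. Finite population correction.** With about 220,000 inhabitants (Setting section), the factor is √((220,000 − 1500)/219,999) = 0.997. It shortens an interval by 0.3% and cannot explain the gap.

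**Step 3. What does produce 0.31–1.05%?**
- 95%, 12/2000: Clopper-Pearson 0.310–1.046%, exact Poisson 0.310–1.048%. Both round to the printed limits.
- 90%, 9/1500: exact Poisson 0.313–1.047%, which rounds to the printed limits; Clopper-Pearson 0.313–1.045%, which rounds to 0.31–1.04% and misses by one unit in the last digit.
- 95% Jeffreys with 0.6% positives: matches for n of roughly 1705 to 1755.

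**Step 4. What the printed limits mean at 9/1500.** If the true prevalence were 0.31%, the chance of 9 or more positives would be 4.7%. If it were 1.05%, the chance of 9 or fewer would be 4.8%. Since 100 − 4.7 − 4.8 = 90.5, the printed limits act as about a 90% exact interval.

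**Step 5. Effect on the under-ascertainment ratio.** Taking the official 0.12% as fixed, the printed limits imply 0.31/0.12 = 2.6 to 1.05/0.12 = 8.8. The exact limits imply 0.2747/0.12 = 2.3 to 1.1359/0.12 = 9.5.

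**The case against.** The strongest defence is that the figure decided nothing. The section says that resources set the size, states no target width, and so gives no sign that 0.27–1.14% would have been found inadequate. The figure of 1500 is a floor, and Recruitment and sample reports that 2145 people were drawn as "a sample representative of the Luebeck population". If all of them took part, 13/2145 would give an exact 95% interval of 0.32–1.03%, slightly tighter than the printed one. The size of the error also depends on the method, and the article names none. This stands, and it keeps the point minor. It does not make the sentence true: the sentence refers to 1500 people, and the article does not say how many of the 2145 attended. That the method is unnamed is no fault in a condensed article, and it does not rescue the figure, because no method tried fits.

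Two stronger readings are tempting, and the documents support neither:
- **The interval was calculated for 2000 people.** The match at 12/2000 is good, but a 90% exact Poisson interval at the stated 1500 rounds to the same limits. Nothing in the article mentions 2000 people or a 90% level.
- **The cohort size rests on this figure, so the study is a third too small.** The interval illustrates precision for a size already set by resources. The step from 1500 to 2000 holds only for the exact methods; a Jeffreys interval would need about 1705 to 1755.

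**Conclusion.** The sentence is wrong as written. The printed 0.31–1.05% cannot be a 95% interval for 0.60% in 1500 people under any of the twelve methods tried. With the exact method the interval is 0.27–1.14%, about 16% wider than printed; the lower limit moves down by about 0.04 and the upper limit up by about 0.09 percentage points. With Wald, Jeffreys, likelihood ratio, mid-P or Wilson the excess width is about 6–11%. Either the sample size or the confidence level appears to be mislabelled, and the documents do not settle which.

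The point is minor: it corrects the only precision figure in the article but alters no sample size, analysis or conclusion. It assumes a two-sided interval and simple binomial sampling, as the sentence implies.

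**What to change.** Restate the sentence as: 0.60% with an exact 95% CI of 0.27–1.14% (n = 1500). If the authors can confirm from their own calculation which input slipped, they may instead keep 0.31–1.05% and print the sample size or confidence level actually used. They should not write 2000 or 90% without that check. Naming the interval method in the same sentence would let readers reproduce it.

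The authors should then confirm that they still regard the precision as appropriate at the corrected width. The cost is one sentence and a slightly less favourable figure; nothing in the design or conduct has to change.

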Limitations of the protocol can arise from its digital nature, as older individuals are less app-savvy or do not possess a smartphone. Participants were asked explicitly about problems answering the questionnaires during their first visit to the study center to mitigate these problems. A support hotline was set up to answer questions and was frequently used.

Initial study results have been published elsewhere and demonstrate vastly underestimated infection rates at the beginning of the pandemic [19]. The official trends of infection rates were well represented in our cohort. However, the absolute numbers were higher due to unrecorded cases. A high retention rate of 75–98% supports the feasibility of large-scale, long-term surveillance studies [19].

For our follow-up examination, we expect the seroprevalence to be remarkably higher than the preceding time points due to the more contagious variant B.1.1.529 (Omicron) and vastly increased infection rates worldwide, including our study area. With a current 7-day incidence rate of more than 1000 infections per 100,000 inhabitants in the municipal area of Luebeck, more than 1% of the overall population is being newly infected with SARS-CoV-2 every week. It needs to be emphasized that, although most cases in vaccinated patients have a mild disease course, there are still approximately 19% unvaccinated inhabitants above the age of four years in Germany at higher risk of severe courses [25]. In other developed countries like the USA or emerging countries, the rates of incompletely vaccinated people are even lower due to a lack of willingness or resources. Only 54% of the population worldwide have been vaccinated [26], which may even be an overestimate. Furthermore, high infection rates with SARS-CoV-2 are likely to aggravate long-term effects of the pandemic, particularly the prevalence of long- or post-COVID-19-syndrome. Although long-term effects occur more frequently in severe cases, up to 2.3% of mild COVID-19 cases show symptoms of post-COVID-19-syndrome more than 12 weeks after infection [27], highlighting the relevance of effective surveillance strategies even in a largely vaccinated population.

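### The stated precision for a 0.60% prevalence in 1500 people (0.31–1.05%) is too narrow even for a perfect test and makes no allowance for test error

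*Protocol article*

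**What the plan says.** The section Sample size calculation in the protocol article opens with "No formal sample size calculation was made" and offers a precision statement in its place. It starts from the fact that "an official COVID-19 prevalence of 120/100,000 inhabitants was reported for the study region", and continues: "The true prevalence was assumed to be 5-fold higher (600/100,000" (per inhabitants). The result is "Based on a 1500 person sample a population-based infection prevalence rate of 0.60" per cent, "with a 95% confidence interval of 0.31–1.05% could be determined". The judgement on this is "The precision of such an estimate seemed appropriate to us".

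The section does not say whether PCR, antibodies or both define infection prevalence, and it mentions no sensitivity or specificity. Laboratory analyses refers the PCR and ELISA methods to an earlier publication.

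Two other places bear on the point. The Discussion says of the first part that "the absolute numbers were higher due to unrecorded cases". For the follow-up, Laboratory analyses says "Serological tests of the second part of the study will be based on dried blood spots (DBS) as sample material", whereas Table 1 lists serum for the in-person visits.

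**The concern.** This statement is the only quantitative support for the sample size, so its figures should follow from its inputs. Two things look wrong.

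First, the limits do not look like those of 9 positives in 1500.

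Second, the interval is placed around the assumed true prevalence, while the study observes test results. At a prevalence this low nearly everyone tested is uninfected, so a small false-positive rate can add a number of positives that is not small beside the true ones. Estimating undetected infections is one of the listed study aims, and the planning factor of 5 (0.60/0.12) is the ratio that false positives would inflate and missed infections would deflate.

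The article also presents its design as a template for other regions, so an optimistic precision figure may be copied.

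**Working it through.** **Inputs from Sample size calculation:** n = 1500, true prevalence π = 0.60%, official prevalence 0.12%, 95% confidence. Expected infected: 1500 × 0.006 = 9. Expected uninfected: 1491.

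**Inputs assumed, because the article gives none:** sensitivity (Se) 95%, with 80% and 100% as alternatives; specificity (Sp) 99.0% to 99.9%.

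**Step 1: reproduce the stated interval with a perfect test.** 95% intervals for 9/1500, in %:

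| Method | Lower | Upper |
|---|---|---|
| Clopper-Pearson (exact) | 0.27 | 1.14 |
| Wilson | 0.32 | 1.14 |
| Jeffreys | 0.30 | 1.09 |
| Mid-P | 0.29 | 1.10 |
| Likelihood ratio | 0.29 | 1.08 |
| Wald | 0.21 | 0.99 |
| Arcsine | 0.27 | 1.05 |
| Logit | 0.31 | 1.15 |
| **Stated** | **0.31** | **1.05** |

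None gives the stated pair, and all are wider than its 0.74 points. The exact interval is 1.136 − 0.275 = 0.86 points wide. The exact 95% interval for 12/2000 is 0.310–1.046%, which rounds to the stated limits. A one-digit slip from the logit limits (0.31–1.15%) would also explain them. The article does not show which happened.

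**Step 2: false positives.** Expected number = 1491 × (1 − Sp). Each 0.1 point of lost specificity adds 1491 × 0.001 = 1.5. With Se 100%, false positives equal the 9 true ones when 1 − Sp = 9/1491 = 0.60%, that is, at a specificity of about 99.4%.

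**Step 3: test-adjusted precision.** Apparent prevalence a = π·Se + (1 − π)(1 − Sp). Clopper-Pearson limits for the expected positives (1500·a, not rounded to a whole number) are converted by Rogan-Gladen, (limit + Sp − 1)/(Se + Sp − 1), and truncated at 0. Positive predictive value (PPV) = π·Se/a. The unadjusted factor is a/0.12%.

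At Se 95%, 9 × 0.95 = 8.55 true positives are expected:

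| Sp | False positives | a | PPV | Adjusted 95% CI | Unadjusted factor |
|---|---|---|---|---|---|
| 99.9% | 1.5 | 0.67% | 85% | 0.23–1.19% | 5.6 |
| 99.5% | 7.5 | 1.07% | 53% | 0.12–1.30% | 8.9 |
| 99.0% | 14.9 | 1.56% | 36% | 0–1.41% | 13.0 |

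Example at 99.5%: a = 0.006 × 0.95 + 0.994 × 0.005 = 0.0057 + 0.00497 = 1.07%; factor 1.067/0.12 = 8.9.

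These intervals treat Se and Sp as known exactly. Uncertainty in validation data would widen them further.

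**Step 4: separate the two causes.** At 99.9% specificity the adjusted interval is about 0.95 points wide, 0.21 more than stated. Of that, 0.86 − 0.74 = 0.12 comes from the interval not reproducing and 0.95 − 0.86 = 0.09 from test error.

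**Step 5: direction of bias.** At Se 80% and Sp 99.9%, a = 0.0048 + 0.000994 = 0.58%, slightly below the true 0.60%. At Se 95% and Sp 100%, a = 0.57%. Upward bias is therefore not inevitable.

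**The case against.** The strongest reply is that the test-error part depends on a specificity the article does not give. At 99.9% there are 1.5 false positives against about 9 true ones, and the interval changes little. A reader might infer that false positives do rival the true ones in this study. The documents do not show that; it would need a specificity near 99.4%. This objection stands, so the size is given only as a range.

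A reader might also infer that prevalence will be reported uncorrected, or that the gap to official counts was wrongly put down to undetected infection. Neither is supported. The article condenses a fuller protocol and refers its assays to a cited publication; validation, confirmatory testing or adjustment may be described there or in an analysis plan. The Discussion sentence on unrecorded cases summarises published results and is not an analysis rule.

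Nor can the 0.6% argument be carried over to the dried blood spots. Time point 8 follows vaccination and the Omicron wave, and the Discussion expects a much higher seroprevalence there. What remains is narrower: specimen type and calendar time change together, so comparison with the serum rounds needs accuracy values specific to the new specimen. The article gives nothing from which to size that effect.

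Finally, the figure is a planning statement for a completed phase with no formal calculation behind it. That limits the consequences. It does not make the interval right, and no later analysis can repair a stated precision that does not follow from its own n.

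**Conclusion.** The point holds in two parts of different strength.

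The firm part needs no outside figure: 0.31–1.05% is not a 95% interval for 9/1500 by any of the usual methods tried. The exact interval is 0.27–1.14%, so the stated width of 0.74 points should be 0.86.

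The conditional part is that the precision was called adequate with no allowance for test error. With sensitivity assumed at 95%, the effect is modest at 99.9% specificity and serious at 99.5% or below, where about half or more of the positives would be false or the lower limit would approach zero. Since prevalence may be defined by PCR, antibodies or both, and their false-positive rates may differ, one specificity range cannot settle the size for this study. Bias in the under-ascertainment factor may run either way.

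The matter is worth correcting, because the statement is the sole numerical basis for the sample size and the correction is cheap. It does not show that the published prevalence is wrong.

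**What to change.** 1. Correct the confidence interval for n = 1500 (exact: 0.27–1.14%), or correct the n if another was meant, and name the interval method.
2. State which test, or combination of tests, defines infection prevalence.
3. Restate the precision with the assumed sensitivity and specificity of that test, as a short range if they are uncertain.
4. Unless an analysis plan not shown already does so, report test-adjusted prevalence (Rogan-Gladen or a Bayesian equivalent) with the uncertainty of the validation data carried into the interval, and base the under-ascertainment factor on it.
5. Separately, when time point 8 is compared with the serum rounds, use a cut-off, sensitivity and specificity established for dried blood spots.

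Requiring a positive result in two consecutive rounds would not be a cost-free substitute for adjustment. It loses transient PCR positives and new positives in the last round, and it keeps sera that cross-react persistently.

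The cost is a less favourable stated precision and a little analysis work. No change to recruitment or sampling is needed.

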#### Data management

The subject and pseudonymized sample data are stored in MySQL databases self-hosted by the University of Luebeck. Access to the database is facilitated by a database web-frontend based on the CRUD database application dadabik™ developed by [name], also self-hosted at the University of Luebeck. An implemented user-rights management system allows for restricted and selective access to the study data. Participants were able to access selected data on a dedicated study website.

## Discussion

To combine and strengthen the activities of German University Medicine to cope with the current pandemic crisis, all 36 university hospitals joined forces nationwide to form the national research network “Network University Medicine” (NUM). The present study is included in the subsection *Nationwide Research Network Applied Surveillance and Testing (B-Fast)* in the population work package (https://www.umg.eu/forschung/corona-forschung/num/b-fast/). This work package tests the feasibility of new innovative surveillance concepts with selected sample testing in regional population clusters to develop best-practice models for surveillance of individuals infected with SARS-CoV-2 with and without symptoms.

Our study protocol allows for comprehensive population-based, prospective cohort surveillance. It also serves as a model for effectively monitoring the long-term dynamics of SARS-CoV-2 infection rates in fixed cohorts, identifying risk factors, and defining effective surveillance strategies. Due to its dynamic nature of mobility, the region of Luebeck is ideally suited as a model region for surveillance of SARS-CoV-2 infections. The used invasive methods are generally safe [24], and the app-based questionnaires make it possible to answer them regularly and remotely. Compared to face-to-face or telephone interviews used in other studies [11, 12], more interviews can be conducted due to the lower survey burden and lower costs. In addition, there is no risk of infection linked to in-person meetings. The test center was designed to minimize the time of stay, and no additional visit is necessary for the follow-up testing at time point 8.

Utilizing an existing app, medical students, and a discount for using the test center infrastructure further lowered the costs per proband. However, complete funding of the study was only secured 7 months after its beginning which posed a significant challenge for a timely study in a highly dynamic situation like a pandemic.

Our approach was well received by study participants, underlined by tight adherence to the questionnaires and very low dropout rates at follow-up testing during the study’s first phase. Another strength is the division of the cohort into both a representative sample of the local population and a group of individuals at greater risk of infection.

Limitations of the protocol can arise from its digital nature, as older individuals are less app-savvy or do not possess a smartphone. Participants were asked explicitly about problems answering the questionnaires during their first visit to the study center to mitigate these problems. A support hotline was set up to answer questions and was frequently used.

Initial study results have been published elsewhere and demonstrate vastly underestimated infection rates at the beginning of the pandemic [19]. The official trends of infection rates were well represented in our cohort. However, the absolute numbers were higher due to unrecorded cases. A high retention rate of 75–98% supports the feasibility of large-scale, long-term surveillance studies [19].

For our follow-up examination, we expect the seroprevalence to be remarkably higher than the preceding time points due to the more contagious variant B.1.1.529 (Omicron) and vastly increased infection rates worldwide, including our study area. With a current 7-day incidence rate of more than 1000 infections per 100,000 inhabitants in the municipal area of Luebeck, more than 1% of the overall population is being newly infected with SARS-CoV-2 every week. It needs to be emphasized that, although most cases in vaccinated patients have a mild disease course, there are still approximately 19% unvaccinated inhabitants above the age of four years in Germany at higher risk of severe courses [25]. In other developed countries like the USA or emerging countries, the rates of incompletely vaccinated people are even lower due to a lack of willingness or resources. Only 54% of the population worldwide have been vaccinated [26], which may even be an overestimate. Furthermore, high infection rates with SARS-CoV-2 are likely to aggravate long-term effects of the pandemic, particularly the prevalence of long- or post-COVID-19-syndrome. Although long-term effects occur more frequently in severe cases, up to 2.3% of mild COVID-19 cases show symptoms of post-COVID-19-syndrome more than 12 weeks after infection [27], highlighting the relevance of effective surveillance strategies even in a largely vaccinated population.

The ELISA cohort and our follow-up study protocol will enable us to study the effects of a sharp increase of SARS-CoV-2 infections on seroprevalence of Anti-SARS-CoV-2 antibodies post-COVID-19-symptoms and possible behavioral, occupational, and medical risk factors. We will be able to monitor the pandemic continuously and discover potential sequelae of an infection in the long term. Further examinations can be easily set up on an ad-hoc basis in the future.

Our study protocol can be adapted to other regions and settings and is easily transferable to other infectious diseases.

